### Recruitment

Patients diagnosed with painful osteoarthritis in the thumb base at the Department of Hand Surgery at Södersjukhuset, Stockholm, are asked to participate in the study.

### Assessment

The Patient-Reported Outcome Measure (PROM) questionnaires at baseline, 3, 6, and 12 months after the first injection and Pain Catastrophizing Scale Questionnaire (PCS [29]) at baseline (to be included as a covariate in the analysis)Objective physical variables (key and pinch grip, MC-1 radial and palmar abduction, opposition): at baseline 3, 6, and 12 months after injection

One doctor performs the preoperative assessment and injection. A second doctor, blinded to the injection type, performs the assessments at 3 and 6 months. Adverse events are reported. At 6 months, treatment is revealed, and blinding is tested by asking the patients and assessor what treatment they believe the patient has received before disclosure. The assessment at 12 months is not blinded. If patients have persisting pain and significant problems at this point, they can proceed with another line of treatment.

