### Outcome

The primary outcome is as follows: change of pain on load (numerical rating scale (NRS) 0–100) in the thumb from before the first injection to 6 months after.

The secondary outcomes are as follows:Change in PROMs (Patient-Reported Outcome Measures) from pre-injection to 3, 6, and 12 months, including Patient-Rated Wrist/Hand Evaluation (PRWHE) score [23], Nelson score [24], and HQ-8 score [25]Objective physical variables: key pinch and three-finger pinch strength measured by using the Saehan Medical® mechanical pinch gauges SH5010 (the mean value of three consecutive measurements is used), radial and palmar abduction of the first metacarpal [26], thumb opposition [27] (Kapandji score). All measurements are performed according to the manual for measuring motion and strength in the Swedish national quality registry HAKIR [26]Time for the patient to experience the need for an intervention in the form of renewed injection, steroid injection, or surgery within 1 year after injection. Any adverse events, complications, and failures (defined as lack of improvement or deterioration of pain) during the study period will be recorded

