### Statistical analyses

For comparing PRP versus placebo, the Wilcoxon signed rank and rank sum tests and chi-square tests will be used for non-parametric data (change in PROMS and non-normally distributed outcomes at different times). The *T*-test will be used for changes in continuous data (objective physical variables) with a normal distribution. Shapiro–Wilk test will be used for establishing data normality. Generalized estimating equations (GEE) will be used to analyze the effect of injection, adjusting for pain catastrophizing, gender, and Eaton class. A Kaplan Meier analysis of the need for another intervention within 1 year will be formed and continuously recorded.

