The sample size is estimated based on the primary outcome, pain on load measured in NRS, which is an established outcome measure in research on musculoskeletal pain [33]. We used the pain on load score in the HQ-8, a questionnaire developed for the Swedish hand surgery quality registry [25]. Pain NRS is a tool that is highly sensitive for individual perception of pain. Therefore, we will adjust the analysis for pain catastrophizing. We have also increased the sample size somewhat to consider the uncertainty of and expected variance of PROMs as outcomes.

The follow-up period is relatively short. The rationale for the primary outcome after 6 months is that with time the risk will increase that the patients require further interventions such as injections or even surgery during the study period. All patients will be assessed after 12 months, but some will have had other treatments by then that may affect the results. Hence, this study will not show long-term effects of PRP. A study with a longer follow-up period to see long-term effect of PRP could be a future perspective if we find PRP effective in the short term.

This is a single-center study. A future improvement could be to include more centers or other osteoarthritic joints to establish that the results are valid also in diverse patient populations.

The foremost strengths of this trial are the size and the randomized double-blinded design.

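### Outcomes measured after allocation is revealed at 6 months (12-month PROMs, 1-year time to intervention) keep the same secondary standing as the blinded outcomes

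*Protocol article*

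**What the plan says.** Four places in the protocol article bear on this.

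- **Assessment.** Blinded assessment ends at 6 months: "A second doctor, blinded to the injection type, performs the assessments at 3 and 6 months". The section continues: "At 6 months, treatment is revealed, and blinding is tested by asking the patients and assessor what treatment they believe the patient has received before" they are told. Of the last visit it says: "The assessment at 12 months is not blinded".
- **Outcome.** The primary outcome is change in pain on load "in the thumb from before the first injection to 6 months after". The secondary outcomes include "Change in PROMs (Patient-Reported Outcome Measures) from pre-injection to 3, 6, and 12 months" and "Time for the patient to experience the need for an intervention in the form of renewed injection, steroid injection, or surgery within 1 year". Neither is divided into a blinded and an unblinded part.
- **Statistical analyses.** Changes in PROMs are compared between PRP and placebo at the different times by rank and chi-square tests. For the time-to-event outcome: "A Kaplan Meier analysis of the need for another intervention within 1 year will be formed and continuously recorded". No censoring or split at disclosure is mentioned.
- **Discussion.** It concedes that by 12 months "some will have had other treatments by then that may affect the results" and that long-term effects will not be shown. It does not name disclosure as a source of bias, and it counts the double-blinded design among the trial's main strengths.

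The Abstract also lists time to intervention within 1 year as a secondary outcome, and says that outcomes are compared between the groups.

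**The concern.** About half of the 1-year window for time to intervention lies after patients know what they received. The event is the need that the patient feels, and a renewed injection counts. A patient who has just learned that the injection was saline has a reason to want something else; a patient told it was PRP has less reason. The 12-month PROMs are self-reported and open to the same influence. The 12-month strength and motion measures are taken without blinding.

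As the plan stands, a 12-month or 1-year difference would be reported with the same standing as the blinded results. It could easily be read as a lasting benefit of PRP when knowledge of allocation may account for part or all of it.

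**Working it through.** **1. The plan's own figure.** The sample size rests on the 6-month outcome: difference 20, SD 30, 80% power, two-sided 5%.

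n = 2 × (1.96 + 0.84)² × 30² / 20² = 2 × 7.85 × 2.25 ≈ 35.3, so 36 per arm. The t-test version gives 36.3, so 37, as stated. This figure is not in dispute, and disclosure does not touch it.

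**2. Timeline.**

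| Result | Before disclosure? |
|---|---|
| Primary, pain on load at 6 months | yes |
| PROMs and physical measures at 3 and 6 months | yes |
| Time to intervention, months 0–6 | yes |
| Time to intervention, months 6–12 | no |
| PROMs and physical measures at 12 months | no |

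**3. Time to intervention (illustration).** From the protocol: 45 per arm and a 1-year window with disclosure at month 6. Assumed, because the protocol gives no rates: no true effect; 15% intervening in each arm before month 6; and the share of those remaining who seek intervention in months 6–12. The log-rank test is also an assumption. At each event, E is the saline share of those at risk and g is 1 for a saline event and 0 otherwise. Z = Σ(g − E) / √ΣE(1 − E), rejecting when |Z| > 1.96.

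Expected events before month 6 are 0.15 × 45 = 6.75 per arm, leaving 38.25 at risk. With 30% vs 10% requests, months 6–12 add 11.5 saline and 3.8 PRP events.

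| Requests in months 6–12, saline vs PRP | Two-sided rejection over 1 year |
|---|---|
| 10% vs 10% | 5% |
| 15% vs 10% | 7% |
| 20% vs 15% | 7% |
| 20% vs 10% | 10–13% |
| 30% vs 20% | 12% |
| 30% vs 10% | 36% |
| 40% vs 10% | 64–65% |

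Ranges are simulation error: for 20% vs 10%, runs of 1,000 to 3,000 trials gave 10–12%, and a run of 20,000 gave 13%. In the 20%, 30% and 40% vs 10% cases, essentially all rejections favour PRP. Censored at 6 months, rejection is about 5% in every scenario.

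A second parametrisation uses 10–20% intervening before month 6, and 10–20% of those remaining afterwards. It multiplies the saline hazard after month 6 by 1.5, 2 or 3. The chance of a significant result favouring PRP is then 6–11%, 10–27% or 23–68%, against a nominal 2.5%.

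**4. 12-month PROMs (illustration).** The protocol's SD of 30 is assumed to apply at 12 months, with 45 per arm, no true effect and a disclosure shift of b points. The noncentrality is (b/30) × √(45/2) = 0.158b, with 88 degrees of freedom. For b = 5, 10 and 15 it is 0.79, 1.58 and 2.37. The chance of a significant result favouring PRP is 12%, 35% and 65%, against a nominal 2.5%. The shifts are assumptions.

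**The case against.** **What stands.**

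- The primary outcome, the sample size and all 3- and 6-month results precede disclosure. A reader might infer that the trial's main conclusion is compromised; the documents do not support that.
- The protocol is open that 12 months is unblinded, limits its question to the short term and disclaims long-term effects. Nowhere does it present the 12-month visit as blinded.
- No log-rank test or hazard ratio is named, and Kaplan-Meier is not among the between-group methods in the Abstract. Comparison by arm is a fair inference from the Abstract and the Statistical analyses section, but the false-positive rates belong to a test assumed here.
- The request rates are assumed. Quoting only the threefold and fourfold gaps would mislead, because small gaps leave the error rate near nominal.
- The direction of bias is plausible but not established. The protocol does not say that saline patients are offered PRP after disclosure.
- A reader might infer that the GEE estimate is contaminated. The protocol does not say which visits enter the model, a detail that may sit in an analysis plan, so this is a conditional remark only.

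**What does not.** The caveats in the Discussion concern other treatments, not knowledge of allocation. None of them changes the standing of the 12-month and 1-year outcomes. Even without a p-value, a two-arm curve that does not mark disclosure invites the wrong reading.

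**Conclusion.** The point holds at moderate severity. Followed as written, the plan gives between-arm results after 6 months, on outcomes that the patient judges, in which an effect of PRP cannot be separated from an effect of knowing the allocation. It does not follow that any late difference is produced by disclosure, or that the bias must favour PRP; the documents show only that both are possible.

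Under the stated assumptions the effect on a 1-year log-rank test runs from near nominal (7%) to large (65%), against about 5% when follow-up is censored at 6 months. The protocol cannot say where in that range the trial would fall. The existence of the problem does not depend on these rates, only on the order of events: disclosure first, patient-judged outcomes afterwards.

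**What to change.** - Make the between-arm comparison up to the 6-month visit, censored at disclosure, the main analysis of time to intervention. Keep the 1-year curve, with the point of disclosure marked and the later part labelled open-label.
- Report 12-month comparisons of PROMs and physical measures as open-label and exploratory, not as evidence of efficacy. They need not be dropped; banning every test after 6 months would be a preference, not a requirement.
- If the GEE includes the 12-month visit, take the treatment effect from the 6-month contrast.
- Name disclosure, alongside other treatments, as a limit on the 12-month results in the Discussion.
- Reconcile the sentence in Assessment on when patients with persisting pain can move to other treatment. It follows the 12-month sentence but could refer to 6 or 12 months, and the answer bears on the shape of the curve.

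**Cost.** The main time-to-intervention comparison has fewer events. Under the illustration with 10% requests in both arms, it has 2 × 6.75 = 13.5 events instead of 13.5 + 2 × 3.825 ≈ 21. The 12-month comparisons lose standing. Visits, care and sample size are unchanged. The change should be made before the analysis, for which data are expected in autumn 2026.

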### Statistical analyses

For comparing PRP versus placebo, the Wilcoxon signed rank and rank sum tests and chi-square tests will be used for non-parametric data (change in PROMS and non-normally distributed outcomes at different times). The *T*-test will be used for changes in continuous data (objective physical variables) with a normal distribution. Shapiro–Wilk test will be used for establishing data normality. Generalized estimating equations (GEE) will be used to analyze the effect of injection, adjusting for pain catastrophizing, gender, and Eaton class. A Kaplan Meier analysis of the need for another intervention within 1 year will be formed and continuously recorded.

### Ethics and data management

The study has been approved by the Swedish Ethical Review Authority, and in accordance with this permit, patients are allowed to withdraw their participation in the study without any reason and without consequence for future care. All participants will fill in an informed consent and have contact information to the research nurse and responsible surgeons should any questions or complications occur. All data are stored according to the ethical permit and is regulated under the GDPR. Data are handled in a pseudonymized form and will be presented on group level. The key to the pseudonyms is stored in a secure location at Södersjukhuset and Karolinska Institutet, only available to the authors. Patients’ insurance is covered by the Swedish Patientförsäkringen.

If patients are unable to attend any follow-up visits, they will be asked to fill out the PROMS online.

Results from the study will be published in a scientific journal and presented at hand surgery meetings.

## Discussion

Osteoarthritis in the base of the thumb is a very common condition. The health of the elderly population is steadily improving. Older people need to remain employable and be self-sufficient well into later life. Hence, this condition warrants further research. There is a lack of scientific evidence for many aspects of the treatment of thumb arthritis, and there is a noticeable need to improve and evaluate treatment outcomes. The James Lind Alliance has identified arthritis in the hand and wrist as one of the 10 most important areas within musculoskeletal diseases to research [30].

In meta-analyses and reviews on osteoarthritis and PRP, the recurrent conclusion is the need for large-size RCTs on this subject [7, 19, 31]. Studies on the effect of PRP can be hard to compare due to a variety of factors—the number of injections, the preparation of the PRP (single or double-spin, centrifugation time, etc.), different joints studied, different severity of the osteoarthritis, different treatments in control groups, etc. In this pragmatic trial that reflects the clinical setting in which PRP injections for thumb base osteoarthritis would be employed, we have chosen to use a commercial kit for extracting the PRP. Hence, we will not know the exact concentration of PRP for each patient. As an autologous blood-derived product, the PRP will differ for every patient.

We compare one dose of high-concentrated PRP (double-spin preparation) with a placebo (saline). The theory is that one injection of high-concentrated PRP is as effective as multiple regular PRP injections, which has been reported to be more effective than a single dose of the regular, single-spin, PRP [32] which is why we have chosen the high-concentration PRP for this study.

We stratify the randomization according to the radiological severity of the disease since previous literature supports a better effect of in the early stages of the osteoarthritis in hand and foot [31].

The sample size is estimated based on the primary outcome, pain on load measured in NRS, which is an established outcome measure in research on musculoskeletal pain [33]. We used the pain on load score in the HQ-8, a questionnaire developed for the Swedish hand surgery quality registry [25]. Pain NRS is a tool that is highly sensitive for individual perception of pain. Therefore, we will adjust the analysis for pain catastrophizing. We have also increased the sample size somewhat to consider the uncertainty of and expected variance of PROMs as outcomes.

The follow-up period is relatively short. The rationale for the primary outcome after 6 months is that with time the risk will increase that the patients require further interventions such as injections or even surgery during the study period. All patients will be assessed after 12 months, but some will have had other treatments by then that may affect the results. Hence, this study will not show long-term effects of PRP. A study with a longer follow-up period to see long-term effect of PRP could be a future perspective if we find PRP effective in the short term.

This is a single-center study. A future improvement could be to include more centers or other osteoarthritic joints to establish that the results are valid also in diverse patient populations.

The foremost strengths of this trial are the size and the randomized double-blinded design.

## Trial status

This is protocol version 1 dated November 21, 2023. Ethical approval was obtained December 11, 2023. The first patient was included January 17, 2024. Predicted final inclusion during the second half of 2025 which entails data ready for analysis in the autumn of 2026.

## Data Availability

Data in this study is restricted by the General Data Protection Regulation (GDPR) (https://www.imy.se/en/organisations/data-protection/). Data can be made be available after pseudonymization for researchers after application to and approval by the Swedish Ethical Review Authority and the local data safety committee at Södersjukhuset ([contact]).

## Abbreviations

CMC-1: The first carpometacarpal joint
PRP: Platelet-rich plasma
APL: Abductor pollicis longus
EPB: Extensor pollicis brevis
STT: Scaphotrapeziotrapezoidal joint
NRS: Numerical rating scale
PROM: Patient-Reported Outcome Measure
PRWHE: Patient-Rated Wrist/Hand Evaluation
HQ-8: HAKIR eight-item participant questionnaire
GEE: Generalized estimating equations
RCT: Randomized controlled study
GDPR: General Data Protection Regulation
SPIRIT: Standard Protocol Items: Recommendations for Interventional Trials
